### Aims of the study

The objectives of this study (see Table 
2) are to evaluate the effect of MDETs on: 1)patient clinical outcomes; 2) the quality of care delivered to patients; and 3) PCPs’ referrals to and patients’ utilization of DEPs. We will also be examining the implementation process of the MDETs and the degree of IPC that occurs between PCPs and MDETs across primary care sites.

### Scientific hypothesis

We hypothesize that the MDET intervention results in the following outcomes at 12 months:

(i) An improvement in patient clinical outcomes, primarily an increase, or greater proportion, of patients in the intervention group who are at target for HbA1c (≤7%) compared to patients in the control group.(Secondary hypothesis: an increase, or greater proportion, of patients in the intervention group who are at target for low-density lipoprotein (LDL-C) ≤2.0 mmol/L, total cholesterol-high density lipoprotein ratio (TC-HDL ratio) < 4.0, and blood pressure ≤ 130/80 mmHg, compared to patients in the control group).

(ii) An increase in the proportion of PCPs performing patient care processes, according to the Canadian clinical practice guidelines for the management of diabetes, in the intervention group compared to the control group.

(iii) An increase in the proportion of referrals to and patients’ utilization of DEPs in the intervention group compared to one year prior to the start of the intervention.

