**Methods/design:**

This study will use a non-blinded, cluster-randomized controlled trial stepped wedge design to evaluate the Mobile Diabetes Education Teams' intervention in improving patient clinical and care process outcomes. A total of 1,200 patient charts at participating primary care sites will be reviewed for data extraction. Eligible patients will be those aged ≥18, who have type 2 diabetes and a hemoglobin A1c (HbA1c) of ≥8%. Clusters (that is, primary care sites) will be randomized to the intervention and control group using a block randomization procedure within practice size as the blocking factor. A stepped wedge design will be used to sequentially roll out the intervention so that all clusters eventually receive the intervention. The time at which each cluster begins the intervention is randomized to one of the four roll out periods (0, 6, 12, and 18 months). Clusters that are randomized into the intervention later will act as the control for those receiving the intervention earlier. The primary outcome measure will be the difference in the proportion of patients who achieve the recommended HbA1c target of ≤7% between intervention and control groups. Qualitative work (in-depth interviews with primary care physicians, MDET educators and patients; and MDET educators’ field notes and debriefing sessions) will be undertaken to assess the implementation process and effectiveness of the MDET intervention.

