### Experimental study design

A non-blinded, cluster-randomized trial stepped wedge design will be used (see Table 
3). Findings from such a study design have been shown to generate sound scientific evidence and may better facilitate the implementation of complex health interventions in practice
[43]. We propose to randomize clusters (that is, primary care sites) and not individuals to the intervention and control group in order to minimize contamination or treatment dissemination between study groups (intervention or control). The presence of a MDET is hypothesized to affect how PCPs care for their patients; and thus, the care patients receive within the same practice site.

**Table 3 T3:** Study design – cluster randomized control trial stepped wedge design treatment schedules

**Randomization of clusters**	**Time 1**	**Time 2**	**Time 3**	**Time 4**	**Time 5**
	**0 months***	**6 months**	**12 months**	**18 months**	**24 months**
Cluster 1	1	1	1	1	1
Cluster 2	0	1	1	1	1
Cluster 3	0	0	1	1	1
Cluster 4	0	0	0	1	1

“*” represents baseline data collection across all sites prior to cluster 1 starting the intervention;

“0” represents control or existing treatment/standard care at primary care sites; “1” represents the MDET intervention; each column represents a data collection point.

Because all PCPs who expressed an interest in this study are eager to have a MDET on site, we plan to use a stepped wedge design to sequentially roll out the intervention. The time at which each cluster begins the intervention is randomized to one of the four roll-out periods (0, 6, 12, and 18 months). The randomization times are separated by six months to allow for assessment of the primary outcome (that is, HbA1c) within a reasonable time after implementation of the intervention

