[13]. Clusters that are randomized into the intervention later will act as the control for the clusters who receive the intervention earlier. All clusters will subsequently receive the intervention, providing additional evidence of the intervention’s effectiveness. Using computer-generated random numbers, the team statistician blinded to the identity of the sites will randomize sites using a block randomization procedure within practice size (determined by the number of PCPs practicing at each site) as the blocking factor. Blocking on practice size will ensure that this site characteristic will be equally distributed across study groups. For the clusters receiving the intervention in the first year, 6 and 12 months of follow-up data collection have been built into the study design (18 and 24 months) to assess the sustainability of the intervention and its effects. See Table 
4 for an overview of data collection outcome measures, methods, participants and timelines.

**Table 4 T4:** Data collection outcome measures, methods, participants and timelines of evaluation study

**Outcome measures**	**Data collection method**	**Participants and timelines**

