### Statistical analysis

All sites will eventually receive the MDET intervention on an ongoing basis following the stepped wedge design, which allows us to evaluate the intervention effect utilizing both within- and between-site information while controlling for underlying time trends (for example, Hussey *et al.*, 2007)
[46]. We plan to sample 20 unique patients/charts per site per time period (1,200 in total), based on the primary hypothesis of a greater proportion of patients reaching the clinically recommended target (HbA1C ≤7%). The proposed sample size will give rise to over 80% power at a significance level of 1% (adjusting for multiple testing) assuming the between-site variation in terms of the coefficient of variation is 0.8. The minimal detectable effect size (expressed as a relative risk) based on the proposed sample is as small as 18%, for baseline proportions “p” in the range of 0.3 to 0.6 (as reported in McCrate *et al.*, 2010
[47], Harris *et al.*, 2005
[7] and Borgermans *et al.*, 2009
[15]]. For example, considering a conservative baseline proportion of *P* = 0.5 and an intraclass correlation (correlation between patients from the same site) of 0.39, we will have 80% power to detect a relative change in proportion of 18% (that is, from 0.5 to 0.59 ((0.59 to 0.5)/0.5 = 0.09/0.5 = 0.18)) attributed to the intervention over a six-month period. We will assess the sample size at the end of the 12 months, and if necessary, the sample size estimation will be adjusted according to established methods described in Chen *et al.* 2004
[48].

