### Quantitative data analysis

Specifically, for Objective #1, we will test the effectiveness of the MDET intervention on clinical outcomes (for example, HbA1C ≤ 7%, LDL-C <2.0 mmol/L) using the generalized linear mixed models (GLMM), which include site as the random effect, time as a fixed effect and the intervention effect. With the GLMM approach, the temporal trends in the effect of the intervention are also evaluated, while the correlations between patients within the same site as well as the variations between sites are accounted for (Hussey *et al.*, 2007)
[46]. The patient-level covariates (for example, age, sex, duration living with diabetes, smoking status) and PCP-level (within sites) covariates (for example, years of practice) will also be included in the model. Hierarchical linear models (HLM)
[49,50] are an important special case of GLMM, and the former name is more commonly seen in the literature for nested data structures (for example, patients at Level 1, PCPs at Level 2 and sites at Level 3). GLMM will facilitate modeling all three level variances in patient outcomes, while utilizing patient variables at Level 1, PCP variables at Level 2 and site variables at Level 3. In addition, we will consider the generalized estimating equations (GEE) approach, which has been suggested to be more robust to misspecification of the variance structure (including. correlations between patients within sites) (Hussey *et al.*, 2007)
[46]. For Objective #2, we will evaluate the effect of the MDET intervention on quality of care delivered to patients (for example, screening for ACR and eGFR) using the GLMM approach, as described for Objective #1, in addition to descriptive summaries (for example, for change in drug dose, PCP years practicing). GLMM will also be used to assess the intervention effect on, for example, the referral rate to DEPs under Objective #3, where the PCPs form the unit of the analyses, and the correlation between PCPs within sites will be taken into account along with the temporal trends of the MDET effects.

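### Hypothesis (i) is set at 12 months, but the listed model has one intervention term with no 12-month contrast and the power is for six months; the three are not reconciled

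*Protocol article*

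**What the plan says.** - Scientific hypothesis: "We hypothesize that the MDET intervention results in the following outcomes at 12 months". Item (i) is the proportion of patients at HbA1c ≤7%, intervention against control.
- Abstract: "The primary outcome measure will be the difference in the proportion of patients who achieve the recommended HbA1c target of ≤7"%, compared between groups. No time point is attached.
- Quantitative data analysis: the clinical outcomes are analysed with generalized linear mixed models, "which include site as the random effect, time as a fixed effect and the intervention effect". The next sentence adds: "With the GLMM approach, the temporal trends in the effect of the intervention are also evaluated". No term for length of exposure is named.
- Statistical analysis: the power example is a change from 0.50 to 0.59 "attributed to the intervention over a six-month period".
- Experimental study design: "The randomization times are separated by six months to allow for assessment of the primary outcome" reasonably soon after implementation. Sites start at 0, 6, 12 or 18 months, and charts are surveyed at 0, 6, 12, 18 and 24 months. The later surveys of early-starting sites serve "to assess the sustainability of the intervention and its effects".
- Table 3 gives cluster 1 a 1 at month 0. Its footnote says the month-0 survey is taken at all sites before cluster 1 begins.

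**The concern.** One primary question has three targets: an effect at 12 months (hypothesis), an effect that is the same at every length of exposure (listed model), and an effect over six months (power). The sentence on temporal trends does not close the gap. A fixed time effect captures the calendar trend shared by all sites, and a single intervention term holds the effect constant. A trend in the effect needs a further term, which is not listed and not linked to hypothesis (i).

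The gap matters if the effect changes with exposure. The single coefficient is then a weighted sum of effects at different exposure lengths, and in a stepped wedge some weights can be negative. The reported estimate could differ from the 12-month effect, and the later surveys intended to show sustainability could pull it away from that effect. Counting start-month surveys as treated makes this worse, because cells with no exposure then enter as treated.

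**Working it through.** **Inputs.** From Statistical analysis: 20 charts per site and survey, 1,200 in total, coefficient of variation 0.8, baseline 0.5, effect 0.09, significance level 1%. From Table 3: four sequences, five surveys. Assumed: two-sided test, linear (risk-difference) approximation, equal sites per sequence, exposure counted from the site's start month.

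- Sites: 1,200 / (20 × 5) = 12, so 3 per sequence. This number is implied, not stated.
- Between-site variance: (0.8 × 0.5)² = 0.16. Within-site variance: 0.5 × 0.5 = 0.25.
- ICC: 0.16 / (0.16 + 0.25) = 0.390, which agrees with the plan's 0.39.

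**Method.** Generalised least squares on site-by-survey means, with five time effects, and V = 0.16 J + (0.25/20) I for each site. The weights are the treatment row of (ΣD′V⁻¹D)⁻¹D′V⁻¹, summed over treated cells by months since start. They add to 1.

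**The plan's own power.** The SE of the single term is 0.0524 under Table 3 coding. Power = Φ(0.09/0.0524 − 2.576) = Φ(−0.86) = 19.5%. The stated 80% is not reproduced with 12 sites and time effects in the model; 48 sites (4,800 charts) give 80.4%. That is a separate matter, and 19.5% serves here as the benchmark.

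**Weights of the single term by months since start.**

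| Coding | 0 | 6 | 12 | 18 | 24 |
|---|---|---|---|---|---|
| Table 3 as printed | 0.99 | 0.495 | -0.03 | -0.26 | -0.195 |
| Only cluster 1, month 0 set to control | 0.74 | 0.62 | 0.00 | -0.24 | -0.12 |
| Actual exposure (all start-month surveys as control) | – | 0.99 | 0.30 | -0.095 | -0.195 |

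**Expected estimate for an assumed ramp** (0 at start, 4.5 points at 6 months, 9 points from 12 months):

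- Table 3: 0.495 × 4.5 + (−0.03 − 0.26 − 0.195) × 9 = 2.23 − 4.37 = about −2.1 points.
- Month-0 cell as control: 0.62 × 4.5 + (0.00 − 0.24 − 0.12) × 9, which is −0.5 points with unrounded weights.
- Actual exposure: 0.99 × 4.5 + (0.30 − 0.095 − 0.195) × 9 = 4.46 + 0.09 = about +4.55 points.

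With an ICC of 0.05 the first and third become −1.2 and +4.9 points. None returns 9.

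**Model with two exposure terms** (6 months; 12 months or more; start-month surveys as control). On the same ramp it returns 4.5 and 9.0 points. The SEs are 0.0524 and 0.0738. Power for 9 points on the second term = Φ(0.09/0.0738 − 2.576) = Φ(−1.36) = about 9%. That term weights exposures of 12, 18 and 24 months by 1.08, 0.14 and −0.22, so it still assumes a constant effect from 12 to 24 months.

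**The case against.** A reader might infer that the 12-month hypothesis is not tested at all, that the model gives 12 months almost no weight, or that a working intervention would yield a null or negative estimate. The documents do not support these as general statements.

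- If the effect is constant once a site starts, which is the usual assumption of the stepped-wedge model the article cites, the single term also estimates the 12-month effect. The ramp is an assumption of this check; the article gives no effect trajectory.
- The near-zero weight and the negative estimates come from counting start-month surveys as treated. Coded by actual exposure, the 12-month weight is 0.30 and the ramp gives a positive but attenuated estimate. If the first treated column already carried six months of exposure, the 12-month weight would be 0.50, or 0.41 with month 0 as control. That reading is hard to square with the stated start months.
- The article does say "the temporal trends in the effect of the intervention are also evaluated". This may condense a time-by-intervention term set out in a fuller plan. Quantitative data collection also foresees extracting up to 12 months of intervention data per chart, which may be how a 12-month outcome is meant to arise.
- Each survey samples different patients, so months since the site started are not months of patient exposure.

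These points remove the strong readings. The mismatch stands: the article itself fixes the hypothesis, the listed terms and the power horizon, and neither the trend sentence nor the extraction window is tied to hypothesis (i).

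**Conclusion.** The point holds as an unreconciled inconsistency that should be fixed. Hypothesis (i) is at 12 months, the listed model has one intervention term without a 12-month contrast, the power is for six months, and Table 3 codes a pre-start survey as treated. The single term answers the 12-month question only under a constant effect from the start.

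The size depends on coding and on the assumed trajectory. The 12-month weight is −0.03 (Table 3) or 0.30 (actual exposure), and exposures of 18 and 24 months have negative weight in both. Under the assumed ramp to 9 points, the expected estimate is about −2 or +4.55 points. These figures rest on 12 sites with 3 per step, 20 charts per cell, variances of 0.16 and 0.25, and a linear approximation. They do not show that the trial would miss a real effect if that effect is immediate and stable.

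**What to change.** 1. Code every survey taken at a site's start month as unexposed, and bring Table 3 into line with its footnote.
2. Choose one target for hypothesis (i):
   - add exposure-duration terms to the mixed model (6 months; 12 months or more), test hypothesis (i) with the 12-month term and keep the single on/off model as a secondary analysis; or
   - keep the on/off term as primary and reword hypothesis (i) to the short-term average effect that it estimates.
3. Restate the power for the chosen target, and name the term that the sentence on temporal trends refers to.

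The edits are to text, but the first option has a real price. The SE rises from about 0.052 to about 0.074, and power for 9 points at two-sided 1% falls from about 19.5% to about 9% with the implied 12 sites. The sponsor should see that figure before choosing. The pooled term also keeps the assumption of a constant effect from 12 to 24 months, which should be stated. The second option keeps the precision but gives up a claim specific to 12 months.

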Many diabetes education programs (DEPs) across Ontario and Canada are starting to provide outreach services by creating collaborative partnerships with local PCPs, and establishing mobile diabetes education teams (MDETs) that deliver DSMS to patients and provide diabetes training and support to PCPs within primary care sites. Models of care that integrate multidisciplinary teams have been shown to improve patient access to DSMS
[19] and increase physician support to reduce clinical inertia in the area of diabetes management in primary care
[20-24]. Furthermore, there is growing evidence that inter-professional collaboration (IPC), whereby professionals from different health disciplines collaborate together to achieve a shared goal, such as quality patient care
[25], can improve patient care processes and health outcomes
[26-42]. Thus, to manage diabetes effectively, alternative models of practice that integrate inter-professional teams may be required to reduce the burden of diabetes.

This protocol is for the evaluation of the implementation of MDETs in primary care in Canada. This model of practice supports PCPs at various primary care sites to assist in and share the care and management of patients with diabetes by offering a MDET (one registered nurse (RN) and one registered dietitian (RD)) onsite, one to four times a month based on patient volume (see Table 
1 for an overview of the MDET intervention). The proposed MDET intervention is informed by the five components of the Chronic Care Model (CCM)
[19]: (i) Organization of integrative patient health care; (ii) Forming community linkages; (iii) Encouraging self-management support; (iv) Providing decision support; and (v) Delivery system redesign (see Table 
2). This article describes the non-blinded, cluster-randomized trial stepped wedge design used in the three-year evaluation study of the MDET intervention in primary care.

**Table 1 T1:** Mobile Diabetes Education Team (MDET) intervention components, timelines and content

**Intervention component**	**Timelines**	**Content**

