RN initial visit	Patient’s first visit with RN, one hour	**Assessment:** Time-span with diabetes; diabetes knowledge; recent hospital admissions; medication regime and adherence; lab blood work review; medical history; blood pressure; foot exam; capacity for SBGM and/or results review; current exercise regime; presence of diabetes complications; risk management for new and existing acute and long-term complications; proper identification of diabetes.
		**Education:** What is diabetes?; how medications work; signs and symptoms of high and low blood sugars; how to reduce long-term complications; benefits of exercise; SBGM technique and timing; how to interpret SBGM results; sharps disposal; stress management; foot care.
		**Teach as needed:** Insulin time action; insulin administration and technique; titrating doses; sick day management; travel glucagon and ketones.
RD initial visit	Patient’s first visit with RD, one hour	**Assessment:** Effects of food, exercise and medications on blood glucose levels and cholesterol; lab blood work review; weight history and goals; fast food consumption; meal composition and timing; specialty foods, supplements, and alcohol use; food allergies; disordered eating.
		**Education:** Healthy eating guidelines; meal planning, food choices and portion size; carbohydrate load and consistency; major food nutrients; specialty food and sweeteners; fiber, fats, sodium, and alcohol; eating out.
		**Teach as needed:** Carbohydrate counting; glycemic index; insulin carbohydrate ratio.
Action plan and goal setting	At initial MDET visits, and ongoing	MDET helps patient find behaviors they would like to initiate or change; patient and MDET collaboratively create action plan and set goals. This may include a referral to a local DEP for additional support (for example, cooking demos, and so on). Goals are then shared with the PCP.
Collaborative patient care/Patient case conferencing	Following each patient visit with MDET	MDET communicates with PCP through face-to-face meetings or using a communication tool to review major obstacles to good diabetes control and make recommendations about medication changes to help improve control for the patient. Goals are decided upon by the patient as what they would like to work on before the next visit, and are reinforced by the PCP on following visits.

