**Diabetes education program (DEP) utilization outcome measures**		
PCP referrals to DEPs	Diabetes education program charts	All patients, 12 months prior to start of intervention to 12 months following start of intervention
Patients’ utilization of DEPs		

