The proportion of patient care processes completed by PCPs over a one-year period (that is, the percentage of patients with tests for HbA1c, blood pressure, lipid profile, screening for nephropathy (ACR and eGFR), foot exams, referrals for dilated retinal exams, and provisions for or recommendations of the flu vaccine) according to clinical practice guidelines will also be collected from patient charts and compared across study groups. We also plan to document and descriptively examine changes to medication (that is, change in drug, drug dose, and addition of another drug) to assess intensification of medical management and whether the diabetes educators had an influence on PCP practices. Descriptive information (that is, sex, age, years practicing) will be collected for each PCP to further assess differences in patient care processes between study groups.

We will also calculate the percentage of patient referrals by PCPs to hosting DEPs and the onsite MDET and compare this to patients’ actual attendance at DEPs and scheduled MDET appointments. The referral rate to DEPs will be compared to the percentage of referrals from participating PCPs and their patients’ attendance at DEPs a year prior to the start of the intervention. Characteristics available in patient medical charts (that is, sex, age, duration of diabetes, clinical information and so on) will be reviewed and compared between those who were and were not referred to the MDET to better understand PCP referral practices. The number of MDET appointments planned for each patient and the number of MDET visits attended will be collected during the intervention period to examine uptake of the MDET intervention.

Various characteristics of team collaboration will be measured using the Collaborative Practice Assessment Tool (CPAT) Version 2

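### Hypothesis (iii) on DEP referral and attendance is framed as an uncontrolled before-after comparison, in conflict with the stepped-wedge model planned for the same objective

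*Protocol article*

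**What the plan says.** **Hypothesis (iii).** Under Scientific hypothesis, (i) and (ii) are set against the control group. Hypothesis (iii), on DEP referral and utilisation, is instead set "in the intervention group compared to one year prior to the start of the intervention". Table 4 gives the matching data window: "All patients, 12 months prior to start of intervention to 12 months following start of intervention". Quantitative data collection repeats the comparison of DEP referral and attendance with the preceding year. It also names referrals to the host DEPs and to the onsite MDET together.

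Statistical analysis says the stepped wedge uses within-site and between-site information while controlling underlying time trends. Quantitative data analysis then plans a generalized linear mixed model (GLMM) for the DEP referral rate under Objective 3, with physicians as the unit, correlation within sites, and time trends in the MDET's effect taken into account.

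**Hypothesis (ii).** It expects "An increase in the proportion of PCPs performing patient care processes". The measure is introduced as "The proportion of patient care processes completed by PCPs over a one-year period" and then spelled out as "the percentage of patients with tests for HbA1c, blood pressure, lipid profile" and further items, including foot examinations. Table 1 lists, within the nurse's first-visit assessment, "medical history; blood pressure; foot exam".

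**The concern.** A before-after contrast at the same sites cannot separate the intervention from whatever else changed over the same two years. Randomised start times exist to make that separation, and hypothesis (iii) as worded does not use them. A rising background in DEP referral would be read as an MDET effect, and a falling one would hide a real effect. Because the analysis section points to a model that could use concurrent controls, the same data could yield two different answers to (iii), with nothing in the article to say which one counts.

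For (ii) the issue is attribution. Two of the listed physician processes are also part of the intervention's own content, so for those items a higher charted rate need not mean that physicians changed their practice.

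**Working it through.** **1. What the before-after contrast estimates.** Let θ be the MDET effect and g a linear background change in referral, in percentage points per year. For a site starting at month s, the windows s−12 to s and s to s+12 have midpoints 12 months apart. The expected difference is therefore θ + g. This holds for every start time, so averaging over the four staggered groups does not cancel it. With g = 5 (assumed) and θ = 0, the contrast reads 5 points.

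**2. Whether concurrent controls exist in the planned data.** Inputs: start months 0, 6, 12 and 18 (Experimental study design) and the window of 12 months either side of start (Table 4).

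| Start | Window (months) | Unexposed | Exposed |
|---|---|---|---|
| 0 | −12 to 12 | −12 to 0 | 0 to 12 |
| 6 | −6 to 18 | −6 to 6 | 6 to 18 |
| 12 | 0 to 24 | 0 to 12 | 12 to 24 |
| 18 | 6 to 30 | 6 to 18 | 18 to 30 |

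By calendar period:

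| Months | Exposed starts | Unexposed starts |
|---|---|---|
| 0 to 6 | 0 | 6, 12 |
| 6 to 12 | 0, 6 | 12, 18 |
| 12 to 18 | 6, 12 | 18 |

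Exposed and unexposed sites overlap throughout months 0 to 18. Within a calendar period both carry the same background level, so a common g drops out of the difference and θ remains.

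**3. How often drift alone would be significant.** The documents give no referral volume or baseline. Assumed: n = 240 or 600 patients in each year, and baseline p of 0.2 or 0.4. The test is two-sided at the protocol's 1% level (z = 2.576), with independent samples and clustering ignored. With drift d and p̄ = p + d/2:

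chance = Φ[(d − 2.576·√(2p̄(1−p̄)/n)) / √((p(1−p) + (p+d)(1−p−d))/n)]

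Example: n = 240, p = 0.2, d = 0.05 gives (0.05 − 2.576 × 0.0381)/0.0380 ≈ −1.27, so a chance of about 0.10.

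| n | p | d = 0.05 | d = 0.10 |
|---|---|---|---|
| 240 | 0.2 | 0.103 | 0.482 |
| 240 | 0.4 | 0.071 | 0.354 |
| 600 | 0.2 | 0.308 | 0.924 |
| 600 | 0.4 | 0.205 | 0.819 |

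With no drift the chance in the upward direction is 0.005.

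**4. Hypothesis (ii), the two overlapping items.** Let b be the physician rate (unchanged) and u the share of sampled patients examined by the nurse, independent of b. If nurse entries are counted, the charted rate is b + (1−b)u. All values are assumed:

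| b | u | Charted rate | Rise (points) |
|---|---|---|---|
| 0.30 | 0.4 | 0.30 + 0.70 × 0.4 = 0.58 | 28 |
| 0.50 | 0.4 | 0.50 + 0.50 × 0.4 = 0.70 | 20 |
| 0.70 | 0.2 | 0.70 + 0.30 × 0.2 = 0.76 | 6 |
| 0.95 | 0.4 | 0.95 + 0.05 × 0.4 = 0.97 | 2 |

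At u = 0, or for a process the nurse does not perform, there is no mechanical rise.

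**The case against.** The strongest reply is that the analysis section already contains the remedy. The design is said to control time trends, a GLMM is planned for Objective 3, and the same family of models is introduced for Objective 1 with time as a fixed effect. The Objective 3 sentence speaks only of trends in the MDET's effect, but very similar wording accompanies the Objective 1 model, where time effects are explicit. It therefore does not show that period effects are absent. This stands: a reader might infer that (iii) is compared only with the previous year, and the article does not support that. What remains is that the hypothesis, Table 4 and the data-collection section all state a before-after comparison. That is a stated choice of comparator, not a detail left to an analysis plan.

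A reader might also take the Background's remark that DEPs "across Ontario and Canada are starting to provide outreach services" as evidence of a referral trend. It describes the spread of mobile teams, that is, of the intervention itself. No trend in DEP referral at sites without a team is reported. The risk is the general one of any before-after comparison.

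On (ii), the article calls the processes physician-completed and never says that nurse examinations are entered in the abstracted chart or counted; that they are is an inference. The overlap is two items. For blood work Table 1 has the nurse only reviewing results, and it does not list her ordering laboratory tests, making retinal referrals or giving flu vaccine. The comparison with randomised controls remains valid for care received from any provider. All of this stands and makes (ii) a minor point.

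**Conclusion.** The concern holds for hypothesis (iii) as a badly fixed comparator and an internal conflict. Three places state an uncontrolled before-after comparison, the analysis section points to a stepped-wedge model, and the article does not say which decides. Under a linear trend the before-after bias equals the yearly background change, in either direction. The significance chances of 7% to 31% (5-point drift) and 35% to 92% (10-point drift) illustrate this on assumed volumes and baselines; they are not estimates for this trial.

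It would go too far to say that hypotheses (ii) and (iii) come out positive even if physicians change nothing. With unchanged referral and no trend, (iii) gives a null result unless referrals generated by the MDET, or referrals to the MDET, are counted. For (ii) the shift runs from 2 to 28 points in the assumed cases and is zero where the nurse does not perform the item. Nor does it follow that the trial cannot judge physician practice, since the other listed processes are not affected in this way. Both points concern secondary objectives; the primary HbA1c comparison is untouched.

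**What to change.** - Reword hypothesis (iii) so that the comparator is sites not yet receiving the intervention, and bring Table 4 and Quantitative data collection into line with Quantitative data analysis.
- Name the stepped-wedge GLMM as the deciding analysis for Objective 3, with fixed calendar-period effects (six-month periods fit the roll-out) and site random effects, using the planned windows of 12 months either side of start.
- Count referrals to DEPs separately from referrals to the onsite MDET. The latter cannot exist before the start, so including them would raise the after-period by construction.
- Keep the before-after figures as descriptive.
- For (ii), record who performed the blood pressure measurement and the foot examination. Score the physician hypothesis on physician entries for these two items, and report completion by any provider as care received.

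The cost is revised wording, tabulation of DEP records by calendar period, and one extra field for two items in a chart review already planned. The change to (iii) needs no new data collection.
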